Not applicable

■ A person who supervises research other than the principal investigator and principal investigator

Not applicable

■ Clinical laboratories, medical and technical departments and institutions related to clinical research

Not applicable

■ Contract Development Organizations

Not applicable

2. Background of clinical research

Parkinson's disease (PD) is a progressive intractable neurological disease characterized mainly by motor symptoms such as tremor, rigidity, akinesia, and postural reflex disorders. Although no curative treatment has been established at this time, the pathology is considered to be abnormal function of the basal ganglia, and as symptomatic treatment, replacement therapy of dopaminergic drugs and neuromodulation to modify the functional abnormality of the basal ganglia. Deep brain stimulation (DBS) therapy for the subthalamic nucleus and globus pallidus has been done. As a result, many of the motor symptoms have become controllable, but there are still treatment-resistant motor symptoms, which are an issue for the future. In particular, "freezing of gait" is a condition in which the sole of the foot becomes stuck to the floor at the start of walking or when changing direction, and is one of the most troublesome symptoms of PD. It is a major cause of falls and a factor that significantly reduces the patient's activities of daily living. In particular, when the drug is on, drug therapy and DBS are completely ineffective, and mechanisms other than dopamine may be involved. Treatment is extremely difficult, and the development of new treatments is desired. Although the pathophysiology of slurring feet has not yet been clarified, it is rooted in impaired gait rhythm due to incontrol of stride length and gait, and in recent years functional MRI analysis has pointed out a decrease in neural activity not only in the basal ganglia but also in the cerebral cortex, supplementary motor cortex and frontal lobe.

Transcranial direct current stimulation (tDCS) is a non-invasive stimulation method in which a weak (0.5 to 2 mA) direct current passes through the skull from an electrode placed on the scalp and modifies cortical excitability directly under the electrode. tDCS can alter brain function to excitatory or inhibitory depending on the polarity of the electrodes placed in the targeted cortical region. That is, under the anode, the cell membrane is depolarized and cortical excitability increases, and under the cathode, hyperpolarization occurs and excitability decreases. Since the effect persists for a certain period of time (from a few minutes to about 1 hour) after the stimulation ends, it has been pointed out that it may also

change the plasticity of synapses. In addition, tDCS is relatively inexpensive for both stimulators and electrodes, and since it is compact, lightweight, and easy to transport, it is possible to stimulate the patient while actually walking. Since tDCS to the primary motor cortex has been reported to enhance voluntary contractions and improve motor function, clinical application in post-stroke rehabilitation has been promoted in Japan in recent years. In this study, tDCS is used to neuromodulate the cerebral cortex (supplementary motor cortex (SMA) stimulation and primary motor cortex (M1)). We will examine the possibility that stimulation can improve freezing of gait. In this study, we used a commercially available tDCS device (Halo Sport) to improve the motor function of athletes. Since this device is relatively inexpensive, compact and lightweight, and can be stimulated while actually walking, we aim to apply this device to the treatment and rehabilitation of freezing of gait.

### 3. Objectives of clinical research

We will examine the possibility of that neuromodulation to the supplementary motor cortex (SMA) or primary motor cortex (M1) by transcranial direct current stimulation (tDCS) improves freezing of gait in Parkinson's disease. If a certain effect is obtained from this research, we would like to lead to the development of a new treatment method for freezing of gait, for example, by combining this method with rehabilitation.

### 4. Target Diseases

#### 4.1. Target Diseases

Parkinson's disease

#### 4.2. Criteria for Determining Target Diseases

Judgment will be made based on MDS diagnostic criteria. In other words, it is essential to have bradykinesia as parkinsonism, and in addition, one or both of resting tremor or muscle stiffness are observed.

### 5. Methods of clinical research

#### 5.1. Clinical study design

Single-arm/open-label/placebo-controlled/single-arm comparison/treatment

#### 5.2. Duration of clinical research

Research period: jRCT publication date to June 30, 2023

Period of patient registration: jRCT publication date to December 31, 2022

#### 5.3. Clinical Research Outline

In the tDCS stimulation used in this study, it is difficult to blind the presence or absence of irritation because the patient feels discomfort in the scalp when the stimulation is actually performed. On the other hand, in order to eliminate the effects of wearing the tDCS device even in a state where no stimulation is performed (sham stimulation), evaluation is performed with sham stimulation and actual stimulation. In general, patients with Parkinson's disease have large motor fluctuations in symptoms due to drug therapy, so the patient's condition may vary depending on the timing of the examination. Therefore, when conducting a stimulation test, it is considered that an appropriate evaluation cannot be performed unless the sham stimulation and the actual stimulus are evaluated as a set.

In this study, we evaluated the efficacy and safety of SMA stimulation for sham stimulation in PART 1 and the efficacy and safety evaluation of M1 stimulation for sham stimulation in PART 2. Two tests will be conducted. In PART 1, participants will first practice various gait assessment without any intervention. Next, the tDCS device is worn on the head for 20 minutes in a resting state (sham stimulation: no actual stimulation), and then the device is removed and gait evaluation is performed. Thereafter, the tDCS device is attached again, SMA stimulation is actually performed at 2 mA for 20 minutes, and then the

device is removed and gait evaluation is performed. This is PART 1. At this point, a decision is made on whether or not to move to PART 2 in consideration of the patient's condition and the feasibility of gait evaluation for each patient. If it is judged that it is possible to migrate, the test of PART 2 will be conducted at an interval of at least 6 hours after the implementation of PART 1. In PART 2, as in PART 1, various gait evaluations are first practiced without any intervention, and then gait evaluation is performed after 20 minutes of sham stimulation with a tDCS device. After that, the tDCS device is attached again, and M1 stimulation is actually performed at 2 mA for 20 minutes, gait evaluation is performed, and PART 2 is completed.

In addition, since previous studies have shown that the increase in cortical excitability by tDCS persists for up to 150 minutes after the end of stimulation, a sufficient washout period of at least 6 hours should be given before PART 1 is completely eliminated before PART 2 tests conduct.

[figure not shown]

## 6. Selection and exclusion criteria for clinical research subjects

Study subjects who meet all of the following inclusion criteria and do not meet any of the exclusion criteria are included.

### 6.1. Criterias of choice

- 1) Male and female patients 20 years of age and older (including age and gender)
- 2) Patients who have been diagnosed with Parkinson's disease who are hospitalized at the Department of Neurosurgery or the Department of Neurology, Juntendo University Hospital for examination or treatment
- 3) Patients with symptoms of freezing of gait
- 4) Patients who have received a sufficient explanation for their participation in this study and have obtained written consent of their own free will after sufficient understanding

### [Rationale]

- 1) It may not be fully understood in minor patients and is highly specific to the disease of interest.
- 2) Because it is a clinical study targeting Parkinson's disease
- 3) Because it is a clinical study for freezing of gait in Parkinson's disease
- 4) Patients who do not have a good understanding in clinical studies or who do not have free

consent are not included

## 6.2. Exclusion Criteria

- 1) Patients with implantable medical devices or electronic devices such as deep brain stimulators, pacemakers or defibrillators
- 2) Patients who are judged by the study physician to have unrelated clinically significant depression or other psychiatric problems
- 3) Patients with injuries or defects in the irritated part of the skull
- 4) Patients with a history of epilepsy or epileptic seizures
- 5) Patients with intracranial metal coils
- 6) Other patients who are judged by the principal investigator to be unsuitable as subjects

### [Rationale]

- 1) Transcranial direct current electrical stimulation may affect implantable medical devices and electronic devices such as deep brain stimulators, pacemakers, and defibrillators.
- 2) Transcranial direct current electrical stimulation may affect psychiatric problems such as clinically significant depression
- 3) If there is an injury or defect in the irritated part of the skull, it may cause stronger stimulation than planned.
- 4) Because it cannot be ruled out that transcranial direct current electrical stimulation can induce epileptic seizures
- 5) Since the possibility of interaction between transcranial direct current electrical stimulation and metal coils cannot be ruled out
- 6) Patients deemed unsuitable as subjects by the principal investigator are not included

## 6.3. Criteria for Transition to PART 2

When the principal investigator or co-investigator determines that there is no problem with the implementation of PART 2 after confirming the patient's general condition and the presence or absence of adverse events after PART 1

## 7. How to register and allocate research subjects

### 7.1. How to register

- 1) Upon registration in this study, the principal investigator or co-investigator shall provide the patient with a sufficient explanation of this study orally and in writing, and obtain written consent to participate in the study. Two copies of the consent form are obtained, one of which is returned to the patient, and the other copy is kept at the department in charge of the medical institution.
- 2) After obtaining consent, eligibility will be confirmed, and cases that are confirmed to meet all of the inclusion criteria and do not fall under any of the exclusion criteria will be enrolled as subjects.
- 3) Patient registration will be conducted by the principal investigator or co-investigator using REDCap, an EDC managed by the university.
- 4) The person in charge of case registration management shall be [name] (Associate Professor, Department of Neurosurgery, Department of Movement Disorder Disease Research and Treatment, Juntendo University).

### 7.2. Randomization method

No assignment was performed in this study.

### 7.3. Blinding

Subjects will be told whether or not they are stimulated and will not be blinded.

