| Study Type                                                                    |                    | Interventional                                                                                                                                                                                                                                                                                                                                                                                                                                                                                                                                                                                                                                                                                                                                                                                                                                                                                                                                                                   |
| Study Design                                                                  |                    | Single arm study / open (masking not used) / placebo control / single assignment / treatment purpose                                                                                                                                                                                                                                                                                                                                                                                                                                                                                                                                                                                                                                                                                                                                                                                                                                                                             |

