## 9. Treatment/Intervention for Clinical Study Subjects

### 9.1. Overview of Pharmaceuticals Used in Clinical Research

#### Transcranial Direct Current Electrical Stimulator (tDCS Instrument)

Brand name : Halo Sport 2

manufacturer : Halo Neuroscience

**Overview** : It is a commercially available headphone-type tDCS device. Three pairs of stimulation pads are attached, which are attached to the crown of the head (M1). The midline pad is on the upper and lower limbs on both the left and right sides, as well as the trunk. The pads on both sides are designed to perform anode stimulation in the left and right hand finger areas. Originally for athlete training and musical instrumentsIt is a device developed to improve skills, has a maximum output of 2.0 mA, and is operated with a smartphone application.1timeIt is designed so that stimulation cannot be done for more than 20 minutes.In addition, it is small and lightweight, and it is possible to stimulate the patient while actually walking.

In this study, with normal attachment to the crown of the head, stimulation from the midline pad M1 stimulation of the upper and lower limbs on both sides and the trunk is possible, and from that state both sides SMA stimulation is possible by shifting in front of 3 cm around the coronal suture. In sham stimulation, All you have to do is attach the device to each part. It doesn't actually stimulate.

**Significant side effects:** This device is actually a commercially available tDCS device, which is widely used by the general public, and its safety is ensured by the design of the stimulator. Stimulation with this device is performed within the scope of the recommendation from the committee of the Japanese Society of Clinical Neurophysiology that stimulation at an intensity of 3 mA for up to 30 minutes is safe, so it is unlikely to cause serious side effects. However, as a side effect, it is expected that you will feel some tingling in the scalp.

[figure not shown]

Halo Sport 2

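### Patients are told when they are stimulated and sham passes no current, so the comparison is not placebo-controlled and cannot separate an effect of the current from a response to knowing about it

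*Protocol*

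**What the plan says.** - **Disclosure.** Protocol 7.3: "Subjects will be told whether or not they are stimulated and will not be blinded".
- **Reason given.** Protocol 5.3 says "it is difficult to blind the presence or absence of irritation because the patient feels discomfort in the scalp when the stimulation is actually performed".
- **What sham is.** Section 9.1: "In sham stimulation, All you have to do is attach the device to each part. It doesn't actually stimulate". Section 5.3 describes the same procedure: "the tDCS device is worn on the head for 20 minutes in a resting state (sham stimulation: no actual stimulation").
- **What sham is for.** Section 5.3 says it is there "in order to eliminate the effects of wearing the tDCS device even in a state where no stimulation is performed (sham stimulation").
- **Design label.** Research Summary, Study Design row: "Single arm study / open (masking not used) / placebo control / single assignment / treatment purpose". The placebo box in the same table is ticked. Section 5.1: "Single-arm/open-label/placebo-controlled/single-arm comparison/treatment".
- **Endpoint and test.** Section 13.1.1 sets the primary endpoint as 30-second walking distance, SMA against sham in PART 1 and M1 against sham in PART 2. Section 15.3 tests the within-patient difference with a one-sample t-test or a Wilcoxon signed rank test.
- **Order.** Sections 5.3 and 10.3 put sham before active stimulation in both PARTs. Section 7.2 says there is no allocation.

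**The concern.** A placebo control is meant to equalise what the patient believes and feels, so that the remaining difference can be credited to the active ingredient. Here the patient knows which condition is which, and sham produces no sensation from current. The protocol's reason for not blinding is that active stimulation is felt. That explains why masking would be imperfect, but it does not explain why the condition must be announced.

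The outcome is a walking test performed by the informed patient, so a response to that knowledge can enter the primary difference. Section 3 asks whether neuromodulation of the SMA or M1 improves freezing of gait, as a step towards a new treatment. A reader who sees the words placebo-controlled would take a positive difference as evidence about the current itself, and the design cannot carry that reading.

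**Working it through.** **1. What the comparison controls.** Setting 5.3, 7.3, 9.1 and 10.3 side by side:

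| Feature | Sham | Active | Matched? |
|---|---|---|---|
| Device worn for 20 minutes | yes | yes | yes |
| Device removed before the gait evaluation | yes | yes | yes |
| Current | none | 2 mA | no (the intended contrast) |
| Scalp sensation from current | none | expected (9.1, 14.2, 19.3) | no |
| Patient told that he or she is stimulated | told no | told yes | no |
| Position in the session | always first | always second | no |

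The intended contrast is the third row. The last three rows differ along with it.

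**2. What the primary difference contains.** For one patient, write D = distance after active minus distance after sham. Then

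D = (effect of current) + (response to knowing or feeling the stimulation) + (order: practice, fatigue, medication timing) + error.

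The test in 15.3 asks whether D is centred on zero. It has no term that separates the first component from the second or third.

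**3. Where masking could help.** Section 10.2 gives four gait evaluations per patient.
- PART 1, sham: the patient has not yet felt the current in this study, so withholding the condition can work.
- PART 1, active: the sensation may reveal it. Section 14.2 lists scalp discomfort as something subjects may experience, and 9.1 and 19.3 expect some tingling.
- PART 2, sham and active: the patient has already felt the current and can recognise its presence or absence.

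Withholding the condition is therefore most useful at one evaluation of four.

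**4. Illustration of size.** The plan has no figure to reproduce: 15.1 says there was too little information for a power calculation, and 20 is a feasibility number. Inputs:
- n = 20 (15.1)
- one-sample t-test (15.3)
- two-sided level of 5% (assumed; not stated in the protocol)
- true effect of the current and order effect both zero (assumed)
- shift d from knowing the condition, in SDs of the paired difference (assumed)

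With 19 degrees of freedom the critical value is 2.093. The noncentrality is d × √20 = 4.472d. The rejection probability is P(|T| > 2.093), with T noncentral t.

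| Assumed d | Noncentrality | Probability of p < 0.05 |
|---|---|---|
| 0 | 0 | 5.0% |
| 0.2 | 0.894 | 13.6% |
| 0.3 | 1.342 | 24.7% |
| 0.5 | 2.236 | 56.5% |

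These are the ordinary power values of this test at these shifts. They show that the test would respond to such a shift as it would to a true effect. They are no evidence that a shift of any given size will occur.

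**The case against.** The best defence is that the choice is open and explained. The protocol says in several places that masking is not used, gives its reason, and limits sham to removing the effect of wearing the device. The study is exploratory (15.1). All of this stands, and nothing is concealed. It does not rescue the placebo-control label, which promises more than the purpose stated in 5.3.

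The second objection is that masking would achieve little, and much of it stands. Sham always comes first. Section 19.5 requires the consent document to cover anticipated risks, so patients will have been told what stimulation may feel like. After the first active period they can recognise it. Giving staff only the evaluation number would hide nothing, because the first evaluation is always sham. Coded reading of the videos would mean up to 20 × 4 = 80 recordings and extra reader time, for a purpose that 15.3 does not give them.

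Three stronger readings are tempting but not supported:
- *That a positive result would be due to expectation.* The documents give neither size nor direction for such a response. They support only that it cannot be separated out.
- *That masking would make a positive result attributable to the current.* The fixed order would remain, and 5.3 itself notes large motor fluctuations with drug therapy.
- *That the staff timing the tests are shown to know the condition.* The protocol does not say what they know. It can be inferred from the open design and fixed order, but it is not stated.

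**Conclusion.** The point holds as a limit on what the comparison can show and as an error in the design label. Disclosure and a no-current sham are both stated outright. It follows that the comparison controls for device wear and rest, but not for expectation or scalp sensation, and that the planned test cannot attribute a positive difference to cortical stimulation alone.

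The size of the problem is unknown. The range of 13.6% to 56.5% depends on assumed shifts of 0.2 to 0.5 SD, an assumed two-sided 5% level, and no effect of current or order. It is an illustration only. That walking distance responds to effort or expectation is a reasonable view of a performance test, not a statement in the protocol.

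The change should be made: the label and conclusion can be corrected fully, the masking only in part.

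**What to change.** 1. **Label and conclusion.** In the Research Summary (Study Design row and placebo box) and in 5.1, replace placebo control with: *open, within-patient comparison with a no-current, device-wearing condition*. In sections 3 and 15.3 add: *a positive difference cannot be attributed to cortical stimulation alone, because the conditions also differ in scalp sensation, in what the patient knows or infers, and in order.*

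2. **Section 7.3.** Replace the disclosure sentence with: *Patients are told at consent that each session includes periods with and without current, but not which period is which or the order. The same script and encouragement are used in both. After each evaluation the patient's guess is recorded, and guesses are reported descriptively.* If this is adopted, the word open and the unmasked entries in the Research Summary and 5.1 should be reworded to describe partial patient masking.

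**Cost.** Protocol and consent wording, review-board approval of the revised consent document (19.4), and one case report form item per evaluation. No extra patients or visits. The downside is that masking is partial: most useful at the PART 1 sham evaluation and largely lost once the current has been felt. It does not remove the order effect, so the limit on the conclusion in item 1 is needed even if item 2 is adopted. If disclosure is kept, item 1 alone is the minimum.
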